**6.2 Place of Study:** The participating health centers will be the Area 18, Area 25, Kawale, and Lighthouse Health Centers. These sites are all government health facilities located in urban Lilongwe, Malawi with ART clinics on their grounds. We selected clinics well matched in terms of staffing levels, services offered, NGO/ancillary program involvement (e.g., all three sites receive training and supervision support from the Lighthouse Trust NGO in Lilongwe), patient volume, and patient population to minimize any important differences between the sites. UNC-Project Malawi will serve as the administrative home for the study and has longstanding relationships with all 4 proposed study sites. UNC Project-Malawi has previously successfully recruited and enrolled adolescents in several sexual and reproductive health studies as well as HIV-related clinical trials.

**6.3 Target Population: ALWH:** We will recruit 105 ALWH from 4 HIV clinics in Lilongwe, Malawi. We aim to recruit for diversity in age, gender identity, and HIV acquisition type. ALWH will be eligible for the study if they are: (1) age 13-19; (2) diagnosed with HIV; (3) scored  $\geq 13$  on the self-reported BDI-II; (4) willing to provide consent (age 18 or 16-17 years old and married (emancipated minors per Malawi law) or assent with parental consent (age 13-17). All HIV+ individuals will be eligible for recruitment including ART initiators, ART re-initiators and established patients. ALWH screening positive for depression who choose not to participate will be referred to a mental health provider.

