Feasibility of ALWH Recruitment: The proposed study will be conducted at 4 comparable, public health centers in Lilongwe District, Malawi: Area 18, Area 25, Kawale, and Lighthouse. Each of the 4 health centers provides ART services, is located in the urban or peri-urban areas of Lilongwe on a main road, and has a monthly ART clinic volume > 115 individuals (age 10-19) who are either initiating care or established patients. We expect 90% will be between the ages of 13-19. Based on studies among ALWH in Malawi, we conservatively estimate 18% will have depression. Assuming an 80% participation rate, enrolling ~6 ALWH presenting with depression (age 13-19) per site per month (35 ALWH total per site) is feasible in 3 months for a total of 105 ALWH in the entire study. Though current government led data collection efforts for ART care in Malawi include adolescents aged 10-19 and our proposed study includes adolescents in a smaller age window (age 13-19), we believe that our conservative recruitment efforts account this mismatch.

Psychosocial Counselor Recruitment: We will recruit 3 young individuals to be psychosocial counselors at each clinic who will provide the 6 individual counseling sessions to participants (approximately 70 sessions per counselor over 4-6 months). Peer Supporter Recruitment: We will recruit 3 peer supporters for the Enhanced FB arm from the Community Advisory Board, Baylor Teen Club Graduates, and YFHS Clinic Experts. We will aim to select peer supporters who are varied in age, gender, and HIV acquisition status. Supervision for the peer supporters will be provided by the study coordinator.

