##### Primary Outcomes:

- Feasibility: will be defined as the ability to successfully enroll and retain depressed ALWH in the study. Feasibility will be assessed as the number of ALWH enrolled, a comparison of planned to actual enrollment and reasons for non-enrollment, and the proportion of ALWH retained in each arm by the end of the study period. We will also assess the number of sessions that participants attended and peer support engagement during the study period.
- Fidelity: will be defined as adherence to the intervention protocol. Fidelity to content for sessions will be assessed by a member of the research team using a checklist of intervention characteristics. Covering at least 80% of checklist items during each session will be considered fidelity to the intervention protocol.
- Acceptability: will be defined as the ability to deliver and participate in a useful intervention that is appropriate regarding resources and culture. Acceptability will be assessed through brief exit interviews with a sample of ALWH, all study staff, and supervisors. Exit interviews will assess how easy the intervention was to participate in or deliver, the perceived usefulness of the intervention, suggestions for improvement, and will explore contextual factors that impeded or facilitated implementation.

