To assess balance across all 3 study arms at enrollment, we will compare participant characteristics using t-tests for continuous variables and chi-square tests for categorical variables. Quantitative Data: Quantitative measures of feasibility, fidelity, acceptability, and preliminary effectiveness will be summarized using means and standard deviations or proportions and compared across arms using statistical models for continuous or binary outcomes, as appropriate. For feasibility, we will examine the mean number of ALWH enrolled and the proportion of ALWH retained in each of the three study arms (adapted, enhanced, and standard of care). For fidelity, we will examine and compare the proportion of counselors covering at least 80% of checklist items during random direct monitoring sessions across study arms. For acceptability, we will examine and compare the proportion of participants and study staff who found the intervention helpful and easy to deliver across study arms. Changes in depression and engagement in care will be assessed for the 6-month study visit and the 12-month study visit. Generalized estimating equations with an appropriate link for each outcome (i.e., identity link for continuous variables and log link for binary variables) and an exchangeable correlation matrix will be used to examine differences in BDI-II scores, engagement in care, and viral suppression and will account for baseline values of all outcomes and clinic differences. All statistical models will control for any unbalanced confounders. Every effort will be made to minimize missing data, including collecting detailed locator information for the participant as well as for up to two individuals who could help reach the participant should they drop out of contact. However, some missing data is likely to occur. We will examine the data for patterns of missingness and if identified, will conduct sensitivity analyses using inverse probability weights to correct for the bias introduced by the missing data. Qualitative data: Analysis of qualitative exit interview data will involve four steps: 1) reading for content; 2) deductive and inductive coding; 3) data display to identify emerging themes; and 4) interpretation. Codes will be refined during the analysis process and memos will be written for each identified theme.

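### Protocol section 6.3: pace, per-site number and duration of recruitment cannot all hold, so the primary feasibility outcome has a clear enrolment total (105) but no usable pace or per-site benchmark

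*Protocol*

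**What the plan says.** The recruitment paragraph of protocol section 6.3 sets the number of sites: "The proposed study will be conducted at 4 comparable, public health centers in Lilongwe District, Malawi". Its inputs per clinic are a monthly volume above 115 patients aged 10 to 19 (new and established), 90% of them aged 13 to 19, 18% with depression, and 80% participation. It concludes that "enrolling ~6 ALWH presenting with depression (age 13-19) per site per month (35 ALWH total per site) is feasible in 3 months", and the sentence ends on a study total of 105.

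That total recurs elsewhere. Section 6.3 opens with "We will recruit 105 ALWH from 4 HIV clinics in Lilongwe, Malawi". Sections 6.1 and 6.5 give three arms of 35, and the budget justification in section 10.1 pays for 105 participants.

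Two other places depend on these figures:
- In section 6.7, the primary feasibility outcome includes "a comparison of planned to actual enrollment and reasons for non-enrollment". It does not say whether the plan means the total, the number per site or the monthly pace.
- The counselor paragraph of section 6.3 plans three counselors per clinic with about 70 sessions each over 4 to 6 months.

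The unit of allocation is also unsettled. The abstract describes individual-level randomization, while sections 2.0, 2.2 and 6.4 say that clinics are randomized. Section 6.1 uses both descriptions.

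**The concern.** One sentence gives a rate, a per-site number, a duration and a total. With the four sites stated just before it, any three of these largely fix the rest, and the stated values do not agree. Enrolment against plan is part of a primary outcome of this pilot, so the disagreement is more than clerical. Suppose 72 participants are enrolled by month 3. That is exactly on plan by the rate and 31% short by the total. A clinic that enrols 26 has supplied its even share of 105 but is 9 short of the stated 35. The per-site figure also appears to set the counselor workload.

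**Working it through.** **Inputs.** All are from section 6.3: 4 sites; about 6 per site per month; 35 per site; 3 months; total 105; and the recruitment inputs >115, 0.90, 0.18 and 0.80. The arm size of 35 and the three arms are from sections 6.1 and 6.5.

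**The plan's total.** 35 per arm × 3 arms = 105. The total is reproduced from the arms.

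**The total from the recruitment figures.**
- Rate × sites × months: 6 × 4 × 3 = 72. Shortfall: (105 − 72)/105 = 31%. With about 6 read as 5.5 to 6.5, the range is 66 to 78.
- Per-site number × sites: 35 × 4 = 140. Excess: (140 − 105)/105 = 33%.
- Rate × months at one site: 6 × 3 = 18, not 35.
- Time for one site to reach 35: 35/6 = 5.8 months, not 3.

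With 3 or 4 sites and 3, 4, 5 or 6 months at 6 per month, only 3 sites for 6 months comes close to 105: 3 × 6 × 6 = 108. Likewise 35 × 3 sites = 105. Section 6.2 names four clinics but in one place still speaks of three sites. A three-site, six-month plan carried over to four sites would explain the figures. That is an inference, not something the protocol states.

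**The rate from the stated inputs.** 115 × 0.90 × 0.18 × 0.80 = 14.9 per site per month. Over 4 sites and 3 months that is 14.904 × 12 = 179. This holds only if each month's attenders are different people. The volume includes established patients, and the text does not say how often they return. The stated 6 is 6/14.9 = 40% of the calculated rate, and no discount is given that would explain it.

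**What would give 105.**
- *Individuals randomized within four clinics, even split:* 105/4 = 26.25 per clinic. At 6 per month: 105/(4 × 6) = 4.4 months. To keep 3 months: 105/(4 × 3) = 8.75 per clinic per month.
- *Clinics randomized:* with four clinics, three arms and at least one clinic per arm, two arms have a single clinic. Each of those clinics must supply 35. At 6 per month: 35/6 = 5.8 months. To keep 3 months: 35/3 = 11.7 per month.

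**Counselor load.** 35 × 6 sessions / 3 counselors = 70, which matches the stated figure. At 26.25 per clinic the same formula gives 52.5. That is a maximum, because it assumes every participant at the clinic is counseled. If two of the three arms are counseled, it is 26.25 × (2/3) × 6/3 = 35.

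**The case against.** The strongest reply is that this is an untidy recruitment narrative and nothing more. The total is 105 wherever it appears, and planned against actual enrolment reads naturally against that total. Section 6.7 sets no pass mark on pace. Sample size, outcome definitions and models are unaffected. On the paragraph's own inputs, about 179 could be enrolled in 3 months, so 105 may well be attainable. Most of this stands, and it limits the point to pace, per-site number and duration. It does not remove the point: the figures still conflict, and a primary outcome refers to the plan. The statistical analysis plan, which was not available, may name the comparator, but it cannot make these figures agree.

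A reader might infer four stronger things that the protocol does not support:
- *That the enrolment benchmark itself is wrong, or recruitment infeasible.* The total is consistent, and the 31% shortfall arises only if about 6 is taken as binding.
- *That the eligible pool is only about 60 (14.9 × 4).* This assumes that the same patients attend every month and nobody new starts care. The protocol gives no visit interval and counts initiators. Both 115 and 18% are low-end inputs; section 2.1 gives depression estimates up to 26%.
- *That the 3-month window drives the calendar and budget.* The work plan in section 9.0 has no 3-month enrolment line. The budget rests on 105 participants, session counts and 12 months of research assistants.
- *That the plan to report "we will examine the mean number of ALWH enrolled" is uninformative because 35 per arm is fixed.* Thirty-five is a target that can be missed, and section 6.7 lists other feasibility measures. A different summary would be a preference.

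Nor can the 35 per site simply be deleted in favour of 26 or 27 per clinic. If clinics are randomized, as section 6.4 says, a clinic alone in its arm does need 35.

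**Conclusion.** The inconsistency is certain, because it is arithmetic within one paragraph. The stated pace yields 31% less than the total, the stated per-site number yields 33% more, and the stated duration is about half the time one site needs to reach 35 at the stated pace. The planned-versus-actual comparison therefore has one sound element, the total of 105, and no usable pace or per-site benchmark.

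The 72 and the 140 need only the stated figures. The 14.9 rests on the unstated assumption that monthly attenders are distinct people. The 26.25 assumes an even split over four clinics. The 35 for a single-clinic arm assumes that clinics are randomized and every arm has at least one. Nothing here shows that 105 is the wrong target or cannot be reached.

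**What to change.** 1. Settle the unit of randomization first, because the per-clinic number depends on it.
2. Restate the recruitment paragraph of section 6.3 with one set of figures that gives 105:
   - *Individuals randomized within four clinics:* about 26 per clinic, with 4.4 months at 6 per clinic per month, or 8.75 per clinic per month if 3 months is kept.
   - *Clinics randomized:* 35 from each clinic that is alone in its arm, with 5.8 months at 6 per month, or 11.7 per month if 3 months is kept.
3. Show how the chosen rate follows from the stated inputs, including any discount, and say whether the monthly volume counts distinct patients.
4. In the feasibility outcome of section 6.7, state that planned enrolment means 105 within the restated period and at the restated pace.
5. Realign the figure of about 70 sessions per counselor if the per-clinic number changes.

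The cost is a few sentences. If the rate of 6 is kept, the stated enrolment period grows by about 1.4 months (4.4 − 3) or 2.8 months (5.8 − 3). Sample size and analysis do not change.

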#### 6.4 Sampling Techniques and Tools

We will recruit ALWH from 4 HIV clinics in Lilongwe, Malawi and each clinic will be randomized to the adapted Friendship Bench, Enhanced Friendship Bench, or standard of care.

#### 6.5 Sample Size Determination

The sample of 105 ALWH (35 per arm) will be sufficient to estimate quantitative measures of feasibility and acceptability with reasonable precision (e.g., confidence intervals around proportions of  $\pm 7$ -9 percentage points across all arms, and  $\pm 9$ -17 percentage points within a given arm).

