#### 6.6 Data Collection Techniques and Tools:

To assess feasibility, sources of data include study visit attendance, counseling session attendance, and peer support engagement logs. To assess acceptability, a brief exit interview and behavioral survey will be conducted. To assess fidelity, a counseling session checklist will be collected. Additionally, to assess preliminary effectiveness, we will measure BDI-II and viral load at enrollment, 6-month visit, and 12-month visit. PHQ-9 will also be measured at enrollment, 6-month visit, 12-month visit, and each counseling session. For viral load testing, trained counselors will collect drops of participant blood from a finger stick prick and put the drops on a blood collection card. The blood spot collection card will be sent to a laboratory to assess viral load and then it will be stored in a freezer at UNC Project Malawi until the end of the study. The collection card will not have the participant's name or other identifying information attached, only their study ID number. Blood collection cards will be destroyed at the end of the study.

Record Availability: The site investigator will make all data abstraction documents and records readily available for inspection by the local IRB as requested.

For the brief exit interview, a semi-structured interview guide will be developed to explore acceptability of the FB and peer support sessions. All interviews will be digitally recorded, transcribed in Chichewa, and then translated into English by study staff according to a transcription protocol. All transcripts will then be reviewed by the interviewer for transcription and translation accuracy.

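### The two precision ranges in section 6.5 do not share a common basis, and the all-arms range cannot apply to intervention acceptability or counseling attendance, which at most 70 participants can inform

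*Protocol*

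**What the plan says.** Protocol section 6.5 is the only justification of the sample size. It says that 105 adolescents, 35 per arm, "will be sufficient to estimate quantitative measures of feasibility and acceptability with reasonable precision". As an example it gives confidence-interval half-widths of ±7 to "9 percentage points across all arms" and ±9 to "17 percentage points within a given arm". It does not state the proportions, the confidence level or the interval method.

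The measures it covers are defined elsewhere:

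- **Feasibility** (section 6.7, Primary Outcomes) includes enrolment, retention by arm, the number of sessions attended and peer support engagement.
- **Acceptability** has two sources. Section 6.6 says: "To assess acceptability, a brief exit interview and behavioral survey will be conducted". Section 6.7, Primary Outcomes, names only "brief exit interviews with a sample of ALWH, all study staff, and supervisors". The number interviewed and the number surveyed are not given.
- **The acceptability analysis** (section 6.7, quantitative data) uses "the proportion of participants and study staff who found the intervention helpful and easy to deliver across study arms".
- **Who receives what.** The budget justification (section 10.1) counts 35 participants with six counseling sessions, and another 35 with six counseling and six peer support sessions. Section 6.1 gives standard of care neither; that arm has usual care enhanced by a study nurse.

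**The concern.** Two things look wrong. First, the pooled sample is three times the arm sample, so at any one proportion the two half-widths must stand in a nearly fixed ratio. The stated ranges do not. Second, section 6.5 offers an all-arms precision for acceptability as well as feasibility, although one arm of three does not receive the intervention being rated or the sessions being attended.

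Section 6.5 covers two of the three primary outcomes, and section 2.2 says the pilot will feed an application for a cluster-randomised trial. Readers of that application will take the stated half-widths as the precision that the pilot delivers for each measure.

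**Working it through.** **Inputs.** n=105 and n=35 (section 6.5); n=70 with counseling and n=35 with peer support (section 10.1). Assumed, because section 6.5 is silent: two-sided 95%, Wald interval, no dropout, independent participants. Half-width = 1.96 × √(p(1−p)/n).

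**Step 1: reproduce each stated range on its own.** Solving p(1−p) = n × (half-width/1.96)²:

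- ±7 at n=105: p(1−p) = 105 × (0.07/1.96)² = 0.134, so p ≈ 0.84.
- ±9 at n=105: p(1−p) = 0.221, so p ≈ 0.67.
- ±9 at n=35: p(1−p) = 0.074, so p ≈ 0.92.
- The maximum at n=35, at p=0.50, is 16.6, which rounds to 17.

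Each range can be reached, but ±7–9 covers proportions of about 67–84% and ±9–17 covers about 50–92%.

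**Step 2: put both on one set of proportions.** At fixed p the per-arm half-width is √(105/35) = √3 = 1.73 times the pooled one. The stated ratios are 9/7 = 1.29 at the lower ends and 17/9 = 1.89 at the upper ends.

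- Keep ±7–9 pooled: per arm 7 × 1.73 = 12.1 and 9 × 1.73 = 15.6, so about ±12–16.
- Keep ±9–17 per arm: pooled 9/1.73 = 5.2 and 16.6/1.73 = 9.6, so about ±5–10.

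**Step 3: try other methods.** Wald, continuity-corrected, t-based, Wilson, Agresti–Coull and Clopper–Pearson intervals were tried at 80%, 90%, 95% and 99%, with rounding, truncation and rounding up, for p from 0.50 to 0.985. None gives 7 (n=105) together with 9 (n=35) at one p. The upper ends can agree: a 95% t-based interval at p=0.60 gives 1.983 × 0.4899/√105 = 9.48 and 2.032 × 0.4899/√35 = 16.8, which round to 9 and 17.

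**Step 4: use the right denominators.** Half-widths in percentage points, 95% Wald:

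| p | n=105 (retention) | n=70 (both active arms) | n=35 (one arm) |
|---|---|---|---|
| 0.50 | 9.6 | 11.7 | 16.6 |
| 0.80 | 7.7 | 9.4 | 13.3 |
| 0.92 | 5.2 | 6.4 | 9.0 |

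At the proportions behind ±7–9, moving from 105 to 70 multiplies by √(105/70) = 1.22: 7 becomes 8.6 and 9 becomes 11.0. Over p = 0.92 to 0.50 the n=70 range is about ±6–12. Peer support exists only in the enhanced arm, so it has ±9–17 at n=35 and no all-arms figure. The counts of 70 and 35 are maxima, before any loss to follow-up.

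**The case against.** Much of the case against is sound.

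- **A reader might infer that the two ranges are impossible.** They are not. Section 6.5 offers them as an example and does not claim common proportions; arm-level proportions could be expected to spread more widely than a pooled one. What stands is that no such basis is stated. In addition, if ±9–17 is kept, the stated lower pooled figure of 7 is pessimistic against 5.2, and the omitted worst case is 9.6 against 9.
- **The per-arm range survives.** It is right for n=35 at proportions of 50–92%. Only the pooled figure needs to change.
- **Session attendance is defined as a count.** The only feasibility proportion that section 6.7 names is retention, which does rest on 105 and 35. The n=70 figure therefore applies only if attendance is reported as a proportion.
- **A reader might infer that acceptability rests on the exit interviews alone.** The Primary Outcomes text says so, but section 6.6 adds the behavioral survey, which could supply the quantitative measure. With an assumed 10 to 20 interviews per arm the half-width at 50% would be 31 to 22 points. That sample size is not in the Protocol, so the actual shortfall below 70 cannot be computed.
- **A reader might infer a definite inflation for clinic randomisation.** Sections 6.1 and 6.4 have clinics randomised, while the abstract and section 6.1 also call the trial individual-level. A factor of √(1+34×ICC) assumes one clinic of 35 per arm, yet four clinics serve three arms and no ICC is given. At an assumed ICC of 0.02, ±16.6 becomes ±21.5 with one clinic of 35, but ±19.1 with two clinics of about 17.5, from √(1+16.5×0.02) = 1.15. Only the direction is supported.
- **The consequence is limited.** The pilot tests no hypothesis, and no progression threshold in the Protocol depends on these half-widths.

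**Conclusion.** The concern holds in a limited form. On a common set of proportions the two ranges disagree, firmly at the lower ends: about ±5–10 with ±9–17, or ±7–9 with about ±12–16. Independently of that, the all-arms range cannot describe intervention acceptability or a counseling-attendance proportion, because at most 70 participants contribute. The pooled half-width is then about ±6–12, with a worst case of 11.7 against the stated 9; at the proportions behind ±7–9 it is 8.6–11.0, some 1.6 to 2.0 points wider. Peer support measures rest on at most 35.

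This assumes 95% Wald intervals, full follow-up and independent participants. That standard of care cannot contribute does not depend on those assumptions. The Protocol does not support saying that the per-arm range is wrong, or putting a figure on the loss from the interview sample or from clustering. The statement is worth correcting because it is the only sample-size justification, but recruitment need not change.

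**What to change.** Restate section 6.5 with the assumed proportions (for example 50–92%), the confidence level, the interval method and a denominator for each measure:

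- retention: ±5–10 overall (n=105) and ±9–17 per arm (n=35);
- participant acceptability, and counseling attendance if reported as a proportion: ±6–12 over both active arms (n=70) and ±9–17 per active arm;
- peer support engagement, if reported as a proportion: ±9–17 (n=35, enhanced arm only).

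In sections 6.6 and 6.7, take the participant acceptability proportion from the behavioral survey and say that all participants in the two Friendship Bench arms complete it. Keep the exit-interview sample for the qualitative analysis. Report the staff proportion on ease of delivery separately, since staff and participants answer different questions.

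If clinics are confirmed as the randomised unit, add that the intervals will be wider still, without a fixed multiplier, because the allocation of four clinics to three arms and the ICC are not given.

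The cost is rewording, possibly one or two items in a survey already planned, and a slightly less favourable stated precision.
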